#### Qualitative data

While qualitative research does not define “outcomes” in the same way as quantitative research, the topics included in the guides for the interviews and focus groups are informed by the logic model framework (see Design section), the outcomes used in the cohort and administrative data research, and findings from the survey. In addition to standard focus group and interview approaches we will use an adapted version of the Most Significant Change technique [43,44] to collect stories of change to answer RQ2. This technique is well suited to interventions where anticipating all changes in advance is difficult. The method involves defining domains of change (e.g. quality of life, mental health, wellbeing), collecting significant stories of change and selecting the most significant of these.

#### Administrative data

Mental health will be indexed via four related measures:

Prevalence of self-reported long term mental health problem (GPPS)Incidence of new depression diagnoses in people age 18+ (QOF)Prevalence of depression in the GP practice population in people age 18+ (QOF)Rate (per 1,000 people in the practice population per month) of antidepressant medication prescriptions (from OpenPrescribing; https://openprescribing.net/)

The main outcome will be prevalence of long-term mental health conditions from GPPS. This measure has the advantage of capturing mental health conditions even if a diagnosis has not been entered in the primary care record (e.g. because of self-referred to IAPT). These data are available at least yearly (although during the COVID-19 pandemic recording of some data, particularly QOF, was suspended).

### Sampling and eligibility

We will use a nested sampling design, recruiting general practices and then recruiting participants from those practice populations. A review of GP patient lists by the Office for National Statistics found them to be a reliable population register [45], making this sampling approach broadly equivalent to a traditional address-based sampling approach.

To define “exposed” and “unexposed” general practices we will use geocoded practice postcodes and practice boundary files to identify practices with addresses within 5km of the route of HS2, and practices with boundaries wholly outside 5km of the proposed route. We will also calculate the percentage of each practice population living within 5km of the route of HS2 using the mid-2020 population estimates for Lower layer Super Output Areas (a administratively-defined geographical area consisting of between 400 and 1,200 households; equivalent to a resident population of 1,000 to 3,000 people) [46]. We will exclude practices with less than 750 registered patients to ensure it is feasible to recruit sufficient participants; this is in line with the criteria the Office for Health Improvement & Disparities applies to determine whether practices are included in public health surveillance data sets (https://fingertips.phe.org.uk/profile/general-practice; accessed 17/06/2022). We will also apply an additional criterion for the “unexposed” practices by aiming to recruit those with similar practice population profiles to the “exposed” practices. For each “exposed” practice we will identify a set of “unexposed” practices with similar practice population characteristics using propensity score matching and aim recruit one of the sets to the study. Within “exposed” or “unexposed” practices, adult patients (aged 18 and over) whose registered residential address falls within the “exposed” or “unexposed” geographical regions, respectively, will be eligible for participation in the cohort data collection.

For the qualitative data collection, GP clinical staff will be recruited from “exposed” practices participating in the study. Other community stakeholders will be identified based on the geographical area served by their organisation and/or its physical proximity to the HS2 route. Local residents will be drawn from cohort participants. The survey data will be used to implement a maximum variation sampling approach to select a diverse set of participants. This approach is suggested for mixed- methods studies where breadth of sampling will complement a quantitative analysis [47]. We will ensure participant diversity on factors including gender, age, ethnicity, employment, education, general practice, distance of their residence from HS2 route, and mental health status.

For the cohort surveys and the qualitative research with local residents, we will aim to engage with the same participants at each of the three planned waves of data collection. However, as this will occur over a 10-year period, we anticipate that there will be loss to follow-up. To mitigate this, we will used a combined longitudinal and repeated cross-sectional approach, which has been used in long-term studies of infrastructure project health impacts to manage participant attrition [48]. This approach is illustrated for two waves in Fig 4. Wave 1 participants will initially be directly invited to participate at subsequent waves, but we will recruit new participants from GP practices to make up for any reduction in cohort size over time.

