### Exposure definition

For complex, geographically-defined interventions, identifying regions exposed to the intervention and measuring the starting point and degree of exposure are not straightforward; exposure definition is an area of ongoing research. For this research, we use postcodes to determine the geographical proximity of the residential address of individual participants and of general practices to the HS2 development. Individuals are defined as “exposed” to HS2 if their postcode of residence is within 5km of the HS2 Phase 2 route. General practices are defined as “exposed” to HS2 if their postcode is within 5km of the HS2 Phase 2 route *and* at least 50% of the population within the practice catchment live 5km or less from the HS2 route. This geographical area is substantially larger than the area eligible for the HS2 homeowner compensation scheme (<1km from the route) [40], but was chosen to ensure capture of broader impacts such as changes to greenspace or road infrastructure. Unexposed general practices are those with a postcode more than 5km away from the entire HS2 route (including Phase 1) *and* with no-one within their catchment living 5km or less from the HS2 route (i.e. no patients who would be considered “exposed” to any part of HS2). Unexposed participants are recruited from these unexposed practices. General practices not meeting “exposed” or “unexposed” definitions were excluded (e.g. any practices with a postcode within 5km of HS2 Phase 2 but with less than 50% of patients meeting the exposure criteria are excluded, or practices with a postcode more than 5km away from the route but with any patients on the practice list living 5km or less from the route).

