### Sample size

#### Cohort data

We aim to survey 6,000 people per wave in four groups (Table 2). General practices through which potential participants will be contacted will be recruited via the National Institute of Health and Care Research Clinical Research Network (CRN).

**Table 2 pone.0298701.t002:** Number of GP practices and participants to be recruited per HS2 route segment and by exposure status.

Route segment		Number of general practices	Number of participants per practice (minimum)	Total number of participants
**Phase 2a**	Exposed	12	100	1,200
	Unexposed	12	100	1,200
**Phase 2b West**	Exposed	6	100	600
	Unexposed	6	100	600
**Phase 2b East**	Exposed	6	100	600
	Unexposed	6	100	600
**Phase 2b amended route**	Exposed	6	100	600
	Unexposed	6	100	600
**Grand total**		60	-	6,000

Inclusion criteria are: participants must be age 18 or older and, for “exposed” participants, have a registered address within 5km of the HS2 route. We will ask general practices to exclude patients who are resident in a care home, terminally ill or receiving palliative care, and practices will also have the discretion to exclude patients for other reasons (e.g. because they have requested not to be contacted about anything not directly related to their care, or because they do not have capacity to consent).

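### Unexposed practices are matched to whole exposed practices, but only exposed patients living within 5km are surveyed, so matching is weakened where the 5km line splits a catchment

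*Protocol article*

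**What the plan says.** Three rules in the protocol article bear on this point.

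- **Matching** (Sampling and eligibility). The team is "aiming to recruit those with similar practice population profiles to the “exposed” practices". For each exposed practice it finds a set of unexposed "practices with similar practice population characteristics using propensity score matching and aim recruit one of the sets to the study". The unit matched is the practice, and the profile is that of the practice population.
- **Who may take part.** Within a practice, only adults "whose registered residential address falls within the “exposed” or “unexposed” geographical regions, respectively, will be eligible for participation in the cohort data collection". The inclusion criteria under Sample size, Cohort data repeat this: participants must, "for “exposed” participants, have a registered address within 5km of the HS2 route".
- **Which practices qualify** (Exposure definition). An exposed practice needs its own postcode within 5km and "at least 50% of the population within the practice catchment live 5km or less from the HS2 route". An unexposed practice must be one "with no-one within their catchment living 5km or less from the HS2 route".

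The team will know how far each catchment is split: "We will also calculate the percentage of each practice population living within 5km of the route of HS2 using the mid-2020 population estimates". The small areas behind this calculation are Lower layer Super Output Areas (LSOAs).

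**The concern.** Taken together, the rules treat the two arms differently. In an unexposed practice, the population that was matched and the population that may be invited are the same by residence. In an exposed practice, up to half of the matched population may be people who cannot be invited.

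Suppose an exposed practice has half its patients in villages near the route and half in a town beyond 5km. A good practice-level match is another half-village, half-town practice. The survey then compares villagers in one arm with a mixture of villagers and townspeople in the other, although the match looked sound.

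The within-wave comparison of exposed and unexposed respondents is at stake first. Analysis plans, Cohort data lists it as one of three main analytical approaches, and it is the only exposed-unexposed contrast that wave 1 of the cohort can offer. The difference-in-differences is at stake only if the two kinds of resident would change differently over time.

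**Working it through.** **The plan's own figure.** With a 3-point difference, SD 8.7, two-sided 0.05 and 90% power, n per group = 2 x (1.960 + 1.282)^2 x 8.7^2 / 3^2 = 176.7, or 177. The t-test version gives 177.7, so the stated 178 is reproduced. The sample size is not in dispute; the 3 points and the SD serve only as a scale below.

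**Inputs**
- s, the share of an exposed practice's catchment population within 5km: 0.5 to 1 by the Exposure definition. Its distribution over the recruited practices is not given.
- g, the difference in mean WEMWBS, in the absence of HS2, between residents inside and outside 5km of the same practice: not given. Assumed here as 1, 2 or 3 points.

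**Mismatch in one practice.** The whole-practice mean is s x (mean inside) + (1 - s) x (mean outside). A perfectly matched unexposed practice has that mean, and all its adults can be surveyed. The exposed arm is drawn from the inside group only. The difference is

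(mean inside) - [s x (mean inside) + (1 - s) x (mean outside)] = (1 - s) x g.

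| s | g = 1 | g = 2 | g = 3 |
|---|---|---|---|
| 0.50 | 0.50 | 1.00 | 1.50 |
| 0.75 | 0.25 | 0.50 | 0.75 |
| 0.90 | 0.10 | 0.20 | 0.30 |
| 1.00 | 0 | 0 | 0 |

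Even at the 50% floor, g would have to be 3 / 0.5 = 6 points for the mismatch to equal the 3-point minimally important difference.

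**Mismatch in an arm.** This is the average of (1 - s) x g over the exposed practices, which number 6 or 12 per route segment (Table 2). If three of six practices sit at s = 0.5 with g = 2 and the other three at s = 1, it is (3 x 1.0 + 3 x 0) / 6 = 0.5 points. If g is +2 in three practices and -2 in the other three, all at s = 0.5, it is 0.

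**What a given arm-level bias would do.** In an unadjusted within-wave test with no true effect, SD 8.7 and clustering ignored, the standard error is 8.7 x sqrt(2/n): 0.502 for 600 per group and 0.355 for 1,200.

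| Arm-level bias | Rejection rate, 600 per group | Rejection rate, 1,200 per group |
|---|---|---|
| 0 | 5% | 5% |
| 0.25 | 8% | 11% |
| 0.5 | 17% | 29% |

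These rates illustrate sensitivity. They are not forecasts for the adjusted analysis.

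**Difference-in-differences.** The same algebra applied to changes gives (1 - s) x (change inside - change outside), again in the absence of HS2. A difference that stays constant over time drops out.

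**The case against.** Much can be said on the other side, and most of it stands.

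- **The main impact analysis is difference-in-differences**, which removes imbalance that is constant over time. The secondary analyses by individual distance use exposed residents only and do not depend on the matched controls. A reader might infer that the mismatch defeats the comparison or that matching is its sole protection; the article supports neither.
- **The models adjust for baseline characteristics and sampling.** A reader might think this helps only for items asked in the survey. It does not stop there: the note to Table 3 says that age, gender and address come from GP records, and an address allows area deprivation and rurality to be attached to each participant.
- **The 50% case is a limit.** A reader might take a full 1-point bias from the table as the bias of an arm. With g = 2, that would need every exposed practice at the floor with the same sign of difference. The article gives no basis for this, and the sign may vary because the part near the route may be the village in one practice and the town in another.
- **Detail is deferred** to protocols on the Open Science Framework, and the caption of Fig 4 speaks of matching both practice and patient recruitment. The unlisted propensity variables are therefore no fault. But the article does state which population the match refers to, and its text describes no patient-level matching.
- **Practice-level matching has merits.** It fits the administrative strand, and measures such as QOF and GPPS results are held by practice. This is a reason to keep such variables in the match, not a reason to take area-based ones from people who cannot be invited.

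The within-wave comparison remains. Difference-in-differences does not protect it, and adjustment corrects it only for the characteristics in the model.

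**Conclusion.** The point holds as a weakness of design. The match refers to the whole practice, while the exposed sample comes from the part of it within 5km, and this affects one arm only. The mismatch is zero where a catchment lies wholly within 5km and grows as the line cuts deeper, up to half of the inside-outside difference.

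Under the assumed g of 1 to 3 points, the size for a single practice runs from 0 to 1.5 WEMWBS points, before adjustment. The arm-level figure is an average that may be much smaller and cannot be computed from the article, because neither g nor the distribution of s is given. The within-wave comparisons bear most of the risk. The difference-in-differences is affected only through differing trends. This is a cheap improvement that makes the matching do what it is meant to do; it does not invalidate the design.

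**What to change.** - **Practices still to be recruited or replaced.** State that the area-based matching variables of each exposed practice (for example age, sex, deprivation and rurality) are computed from its LSOAs within 5km. Keep practice-level variables where no small-area version exists.
- **Wave 1 practices already recruited.** Practice recruitment began in March 2023 and mailing in May 2023, so the match cannot be redone. Report the distribution of s, and check covariate balance among eligible or surveyed residents. Then either weight unexposed respondents to the within-5km profile of their matched exposed practice or adjust for those variables individually. Do this in the within-wave and the difference-in-differences models.

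The cost is some recoding of the match, area-level proxies for some practice measures and, if weights are used, a small loss of precision. The LSOA estimates are already in use to calculate the share within 5km, and the recruitment targets need not change.

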**Fig 4 pone.0298701.g004:**
[figure not shown]
Overview of sampling approach, simplified to illustrate case/control matching of general practice (GP) and patient (P) recruitment for a single exposed practice over two waves of data collection. White circles indicate drop-out at wave 2; squares indicates new patients recruited at wave 2.

### Sample size

#### Cohort data

We aim to survey 6,000 people per wave in four groups (Table 2). General practices through which potential participants will be contacted will be recruited via the National Institute of Health and Care Research Clinical Research Network (CRN).

**Table 2 pone.0298701.t002:** Number of GP practices and participants to be recruited per HS2 route segment and by exposure status.

Route segment		Number of general practices	Number of participants per practice (minimum)	Total number of participants
**Phase 2a**	Exposed	12	100	1,200
	Unexposed	12	100	1,200
**Phase 2b West**	Exposed	6	100	600
	Unexposed	6	100	600
**Phase 2b East**	Exposed	6	100	600
	Unexposed	6	100	600
**Phase 2b amended route**	Exposed	6	100	600
	Unexposed	6	100	600
**Grand total**		60	-	6,000

Inclusion criteria are: participants must be age 18 or older and, for “exposed” participants, have a registered address within 5km of the HS2 route. We will ask general practices to exclude patients who are resident in a care home, terminally ill or receiving palliative care, and practices will also have the discretion to exclude patients for other reasons (e.g. because they have requested not to be contacted about anything not directly related to their care, or because they do not have capacity to consent).

#### Qualitative data

For local residents we will conduct eight focus groups per data collection wave, two from each part of the Phase 2 route (Phase 2a Phase 2b West, Phase 2b East, and the section of Phase 2b East that is not proceeding as originally planned), offering one virtual and one in-person focus group to participants from each route section. Each focus group will include a maximum of 10 participants. We will also conduct 3–4 interviews for each route segment. We will conduct up to 53 interviews per data collection wave with clinical staff from participating exposed GP practices and community stakeholder representatives. These sample sizes have been determined in collaboration with the funder and should be sufficient to reach thematic saturation.

#### Administrative data

We will include all general practices in England that have at least 750 registered patients for at least one year during the study period, including those that were active from 2013 onwards. This will result in a total sample of approximately 8,000 practices (in 2013), about 1,000 of which meet the criteria for being “exposed” to the HS2 development. These numbers are approximate because the exact number of practices changes each year as practices close down or merge with others, and new practices open.

### Data collection

#### Cohort data

Potential participants will be contacted via their general practices using a secure mailing service that is commonly used by practices for mailouts. This approach ensures that the research team will not have access to any personal identifying information before individuals have consented to participate in the study. Potential participants will receive a cover letter, participant information sheet, consent form, refusal slip, paper survey booklet, and pre-paid reply envelope in the post. Participants will have the option to complete the refusal slip or consent form and survey using the paper forms or using an online platform (Qualtrics). If preferred, participants will be able to schedule a telephone interview with the research team in which they will go through the survey over the telephone and the staff member enters their responses into the online survey for them. Recruitment for each practice will be open for at least two months, therefore participants have this length of time to decide whether they would like to participate. If required due to low participation rates, one reminder will be sent via text message containing a greeting, a personalised link to the survey.

Survey questions for wave 1 have been selected to reflect the outcomes and potential explanatory factors highlighted in the WISH2 logic model. Where possible, we have used questions from national surveys as this will enable us to compare our data with national estimates. An overview of the topics to be covered and question sources is provided in Table 3.

**Table 3 pone.0298701.t003:** Overview of topics covered in the WISH2 survey and sources of questions used.

Area	Topics covered	Question sources
Impact of HS2	• Awareness of HS2 development • Perspectives on individual and community impact	• WISH2 team–developed in collaboration with the PAG
Health, wellbeing and healthcare use	• Mental wellbeing • Physical and mental health conditions • Health and social care service use • Sleep quality • Alcohol use	• Warwick-Edinburgh Mental Wellbeing Scale (WEMWBS) [49] • EuroQol-5D [50] • General Practice Patient Survey [51] • Social and Community Opportunities Profile [13,17,18] • National Health Sleep Awareness Project [52] • Alcohol Use Disorders Test [53]
Community and social inclusion	• Social networks • Financial wellbeing and employment	• Social and Community Opportunities Profile [13,17,18]
Socio-demographic	• Employment • Caring responsibilities • Transport use • Ethnicity • Household size	• Understanding Society [54] • Social and Community Opportunities Profile [13,17,18] • NatCen National Transport Survey [55] • General Practice Patient Survey [51] Note: Age, gender, and address will be available from GP records so have not been included here to reduce participant burden.

Consent for access to medical record data (practice data and IAPT data) will be sought from participants at baseline, as well as consent to re-contact for study updates and follow-up. Participants will also be asked to indicate whether they would be willing to participate in interviews or focus groups as part of the study.

#### Qualitative data

Participants selected from the study cohort will be invited to participate in a focus group or interview via telephone, email, or post (for survey participants, based on indicated communication preferences in their survey consent form). Other potential participants (clinical staff and community stakeholders) will be invited by email or telephone. Participants will receive an information sheet and consent form in advance and a list of dates and local venues (for focus groups) or tailored arrangements (for interviews). Each focus group will take up to 120 minutes and interviews up to 60 minutes. In addition to standard focus group and interview approaches, we will use an adapted version of the Most Significant Change technique [43,44]. Focus groups and interviews will be used to collect stories of change. Stories may be recorded with participants’ consent and transcribed verbatim. Recordings will be deleted once transcripts have been finalised. a combination of direct (interviewee’s experience) and indirect (interviewee relating stories of others’ experiences).

